**STUDY TITLE**

Comparing diagnostic accuracy of **H**igh-end intestinal **U**ltrasound versus **M**id-end ultrasound with tandem **I**leo-colonoscopy in inflammatory bowel **D**isease (the **HUMID** study): a paired, validating confirmatory study

**SITE OF STUDY**

Asian Institute of Gastroenterology, Somajiguda, Hyderabad

1. **INTRODUCTION**

Inflammatory bowel disease (IBD), comprising Crohn’s disease (CD) and ulcerative colitis (UC), is a chronic, relapsing condition that requires accurate and timely diagnosis for effective management. The gold standard for assessing disease activity includes ileo-colonoscopy and cross-sectional imaging, both of which are costly and often inaccessible in resource-limited settings. Point-of-care ultrasound (POCUS) has emerged as a valuable, cost-effective alternative for managing IBD, particularly in low-resource environments.

Our previous research using a mid-end ultrasound machine (Siemens ACUSON S2000) demonstrated that POCUS significantly influenced clinical management, helping to avoid colonoscopy in more than half of the cases.[1] The study found that POCUS, when compared to ileo-colonoscopy, had a sensitivity of 80% and a specificity of 94.4% for CD, and a sensitivity of 80.8% and a specificity of 92.8% for UC. These results highlight the potential of POCUS to serve as an essential diagnostic tool in the management of IBD, particularly in settings where access to advanced diagnostic modalities is limited.[1]

While mid-end ultrasound machines have shown promise in managing IBD, there is a lack of comparative studies evaluating their diagnostic accuracy against high-end machines. High-end ultrasound devices, offer advanced imaging features such as extended field of view, speckle reduction, and enhanced computing power, which could potentially improve diagnostic accuracy. However, their high cost poses a significant barrier to widespread use, especially in resource-limited settings.

**2.0 RATIONALE**

The HUMID study addresses the critical need to evaluate the diagnostic accuracy of mid-end versus high-end intestinal ultrasound (IUS) machines in the context of inflammatory bowel disease (IBD) with ileocolonic involvement. In resource-limited settings, access to advanced diagnostic tools such as colonoscopy and cross-sectional imaging is often scarce, making point-of-care ultrasound (POCUS) an essential, cost-effective alternative for managing IBD.[2] While high-end ultrasound machines offer superior imaging quality through advanced features such as extended field of view, speckle reduction, and enhanced computing power, their high procurement costs limit their accessibility. Mid-end machines, equipped with high-frequency probes (≥5 MHz), provide a more affordable option, potentially enabling broader dissemination of POCUS in settings where resources are constrained. However, there is a perceived gap in the diagnostic precision of mid-end machines, as current literature on their efficacy remains limited. This study seeks to validate whether mid-end ultrasound machines can reliably match the diagnostic accuracy of high-end machines when compared to the gold standard of ileo-colonoscopy, ultimately aiming to inform resource allocation and optimize IBD management in diverse healthcare environments.

1. **STUDY OBJECTIVES**

**3a. Primary objective**

To compare the diagnostic accuracy of intestinal ultrasound (IUS) using a high-end ultrasound machine versus a mid-end ultrasound machine in relation to ileo-colonoscopy for assessing ileocolonic involvement in IBD.

**Secondary Objectives:**

To evaluate changes in clinical management decisions following IUS with a high-end ultrasound machine compared to a mid-end machine.

**4.0 STUDY POPULATIONS**

**Inclusion Criteria:** Adult patients (18-75 years) with a confirmed diagnosis of IBD (CD or UC) involving colon and/or terminal ileum who are attending outpatient or inpatient care at the Asian Institute of Gastroenterology.

**Exclusion Criteria:** Patients with known contraindications to colonoscopy, pregnant women, and those unable to provide informed consent.

**5.0 DESIGN AND DURATION OF THE STUDY**

Cross-sectional study, follow up until ileo-colonoscopy (same or next day)

Duration of study (Recruitment period) : 6-12 months (estimated sample size 100)

**6.0 METHODOLOGY**

The HUMID (High-end vs. Mid-end Ultrasound in IBD Diagnostics) study is a prospective, paired, validating confirmatory study aimed at comparing the diagnostic accuracy of mid-end versus high-end intestinal ultrasound (IUS) machines in patients with inflammatory bowel disease (IBD) involving the ileocolonic region. The study specifically contrasts the performance of the mid-end Siemens ACUSON S2000 and the high-end Samsung RS85 ultrasound machines, using ileo-colonoscopy as the reference standard.

Upon enrollment, each patient will undergo a clinical assessment by an IBD specialist using the Harvey–Bradshaw Index (HBI) for Crohn’s Disease (CD) and the Simple Clinical Colitis Activity Index (SCCAI) for Ulcerative Colitis (UC). Patients will be categorized into three groups: flare/relapse, response to new therapy, and clinically quiescent disease. Point-of-care ultrasound (POCUS) will be performed using both the Siemens ACUSON S2000 (mid-end) and Samsung RS85 (high-end) machines, with patients asked to fast prior to the examination, though this is not mandatory. The Siemens ACUSON S2000 will utilize a high-frequency linear probe (9 L4, 4–9 MHz) and will use pediatric abdomen and thyroid presets with a trapezoid view for bowel visualization. The Samsung RS85 will employ linear 2-10 MHz and 2-18 MHz probes, offering advanced imaging features such as extended field of view and speckle reduction. Both ultrasound examinations will be conducted jointly by a GI sonologist and an IBD specialist, with findings documented by a research associate and consensus reached by the examiners. Ileo-colonoscopy will be performed on the same or following day if clinically indicated, providing the diagnostic gold standard against which the accuracy of both ultrasound machines will be assessed.

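### The colonoscopy follows both scans within a day, with no masking of the endoscopist and no locking of the scan reads, so review bias is uncontrolled and can distort the machine comparison in either direction

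*Protocol*

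**What the plan says.** Section 6.0 of the protocol sets out the sequence.

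- Clinical step: "Upon enrollment, each patient will undergo a clinical assessment by an IBD specialist", using HBI for Crohn's disease and SCCAI for ulcerative colitis. "Patients will be categorized into three groups: flare/relapse, response to new therapy, and clinically quiescent disease".
- Scans: "Both ultrasound examinations will be conducted jointly by a GI sonologist and an IBD specialist". On how a result is settled, the protocol says only "with findings documented by a research associate and consensus reached by the examiners".
- Reference: "Ileo-colonoscopy will be performed on the same or following day if clinically indicated". The role given to that examination is "providing the diagnostic gold standard against which the accuracy of both ultrasound machines will be assessed".

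The primary objective (3a) is comparative: "To compare the diagnostic accuracy of intestinal ultrasound (IUS) using a high-end ultrasound machine versus a mid-end ultrasound machine", each in relation to ileo-colonoscopy. The secondary objective is change in management decisions after the scan, and section 7.0 counts patients whose management was altered by scan findings.

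The protocol does not say who performs the colonoscopy, whether that person has seen the scans, or whether the reads are fixed beforehand. Item 5 of section 10.0 gives a general assurance of objectivity that rests on a multidisciplinary team; it describes no masking.

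**The concern.** Sensitivity and specificity mean what they should only if the reference is read without knowledge of the test under study. Here the reference comes hours to a day after the scans. The scan findings are meant to inform care, so they may plausibly reach the treating team before the endoscopy is read. Sections 6.0 and 7.0 give no threshold for a positive scan or a positive colonoscopy, which leaves room for borderline endoscopic calls to move towards a known scan result.

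The machine comparison is what is chiefly at stake. Section 10.0 would use a finding that the mid-end machine performs as well as the high-end one to support its wider adoption. An endoscopist who knows one scan better than the other, or trusts it more, can create or hide a difference.

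This cannot be left to an analysis plan. Who sees what, and when, is study conduct, and no later analysis can restore the independence of a colonoscopy that has been read unmasked.

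**Working it through.** The protocol gives no figure for this bias, so there is nothing to reproduce. The calculation below is illustrative and shows direction and range only.

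**Inputs**

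- From the Introduction, the earlier mid-end study "had a sensitivity of 80% and a specificity of 94.4% for CD, and a sensitivity of 80.8% and a specificity of 92.8% for UC".
- Assumed: prevalence of active disease among patients who have a colonoscopy (0.5, varied from 0.3 to 0.7).
- Assumed: *f*, the share of reference calls disagreeing with the scan that are moved to agree with it (0.10 to 0.50).

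**One machine**

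Start from the true cells TP, FN, TN and FP. Moving a share *f* of the disagreeing calls gives

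- Se' = (TP + f·FP) / [TP + f·FP + (1 − f)·FN]
- Sp' = (TN + f·FN) / [TN + f·FN + (1 − f)·FP]

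For the Crohn's disease figures at prevalence 0.5: TP = 0.400, FN = 0.100, TN = 0.472, FP = 0.028.

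| f | Se' | Sp' |
|---|---|---|
| 0 | 80.0% | 94.4% |
| 0.10 | 0.4028/0.4928 = 81.7% | 0.4820/0.5072 = 95.0% |
| 0.25 | 0.4070/0.4820 = 84.4% | 0.4970/0.5180 = 95.9% |
| 0.50 | 0.4140/0.4640 = 89.2% | 0.5220/0.5360 = 97.4% |

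Prevalence matters little: at f = 0.25, sensitivity runs from 84.3% to 84.7% and specificity from 95.8% to 96.2% over prevalences of 0.3 to 0.7. The ulcerative colitis figures (80.8%/92.8%) become 85.2%/94.8% at f = 0.25 and prevalence 0.5.

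**Two machines**

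Further assumptions: true sensitivity 80% (mid-end) and 90% (high-end), a gap of 10 points; specificity 94.4% for both; errors independent given true status; prevalence 0.5.

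Suppose the endoscopist follows the mid-end scan at f = 0.25. Reference positives are 0.400 + 0.75 × 0.100 + 0.25 × 0.028 = 0.482. Mid-end sensitivity is (0.400 + 0.007)/0.482 = 84.4%. High-end sensitivity is (0.475 × 0.90 + 0.007 × 0.056)/0.482 = 88.8%. The other rows follow in the same way.

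| Endoscopist follows (f = 0.25) | Mid-end Se | High-end Se | Gap (points) |
|---|---|---|---|
| Neither (masked) | 80.0% | 90.0% | 10.0 |
| Mid-end scan | 84.4% | 88.8% | 4.3 |
| High-end scan | 78.9% | 92.4% | 13.5 |
| A positive on either machine | 79.6% | 89.4% | 9.8 |
| Both, only where they agree | 80.4% | 90.5% | 10.0 |

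Gaps are taken from unrounded values. When the mid-end scan is followed, the gap is 7.8 points at f = 0.10 and −1.8 at f = 0.50. When the high-end scan is followed, it is 11.4 and 17.0.

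The scan that is followed gains. The other can lose, and the gap can move either way.

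**The case against.** The strongest reply is that silence is not evidence of bias. The protocol does not say who performs the colonoscopy, and the site may already separate the roles. That is correct, and it limits the point to an uncontrolled risk. Three stronger readings are tempting, and the document supports none of them.

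- *One person scores, scans and scopes.* The text names the same role for the clinical assessment and the scans, but does not say that it is the same individual, and it does not identify the endoscopist.
- *Accuracy is inflated for both machines and the difference between them narrows.* The one-machine calculation cannot show this, and the two-machine calculation contradicts it as a general statement: a machine that is not followed can lose sensitivity, and the gap can grow.
- *Knowledge of HBI or SCCAI makes test and reference dependent.* A scan reader who knows the clinical score does not thereby know the colonoscopy result. Such knowledge may raise sensitivity at the expense of specificity, which is a different bias from an endoscopist knowing the scan.

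It is also fair to say that a point-of-care scan with an IBD specialist present is normally done with clinical information to hand. Masking the readers to it would change the test being evaluated. That part of the objection stands: reader access to clinical scores is a choice to be declared, not a defect.

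The reply leaves the main point untouched. The protocol contains nothing that keeps the scan findings from the endoscopist or fixes the reads beforehand.

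**Conclusion.** The point holds as an unprotected design step that should be changed. Followed as written, section 6.0 leaves the reference standard open to review bias. The expected direction is upward for whichever scan the endoscopist follows; for the primary comparison the direction is unknown.

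The size cannot be derived from the document, because *f* is not given. Under the one-machine assumptions, the rise is 1.7 points in sensitivity and 0.6 in specificity at f = 0.10, and 9.2 and 3.0 points at f = 0.50. Under the two-machine assumptions, a quarter of disagreeing calls moved turns a 10-point gap into anything from 4.3 to 13.5 points, so the distortion can be of the same order as a difference worth detecting. Both results apply only to patients who have a colonoscopy, which the protocol makes conditional on clinical indication.

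**What to change.** Add to section 6.0:

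1. Each machine's read is recorded and locked before the colonoscopy begins.
2. The endoscopist for a study patient took no part in that patient's scans and does not see the scan record until the endoscopic findings are entered.
3. Findings needed for the patient's safety may be disclosed. Such cases are logged as unmasked and excluded in a sensitivity analysis.
4. State, as part of the definition of the index test, whether scan readers know HBI/SCCAI and the clinical category, and apply the same rule to both machines. Masking the readers is not required.

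The cost is some rostering among existing specialists and one form-locking step. No patient procedure is added.

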**8.0 SAMPLE SIZE CALCULATION**

This is a pilot study and hence we plan to recruit 100 patients to have a reasonable sample size for achieving clinical significance

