   - **Confidentiality:** Patient confidentiality will be rigorously protected. All data collected will be anonymized and securely stored, ensuring privacy and ethical handling of patient information.
4. **Clinical Relevance and Utility:**
   - **Direct Clinical Impact:** The study’s outcomes will have immediate clinical applications. If the mid-end ultrasound proves to be as effective as the high-end model, it could facilitate broader adoption of ultrasound technology in settings with limited resources, thus improving patient care and diagnostic efficiency.
5. **Multidisciplinary Approach:**
   - **Comprehensive Evaluation:** The study involves a multidisciplinary team of gastroenterologists, ultrasound specialists, and researchers, ensuring a thorough and objective evaluation of the imaging techniques.

In summary, the HUMID study is ethically justified as it seeks to enhance patient care by validating a cost-effective diagnostic tool, potentially reducing the reliance on invasive procedures, and improving the management of inflammatory bowel disease. The study’s design incorporates thorough informed consent, minimizes risk, and maintains confidentiality, further supporting its ethical integrity.

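### Both machines are scanned jointly with consensus findings, and no scan order, masking or locking of the first result is set, so the first scan can inform the second and bias the comparison towards agreement

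*Protocol*

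**What the plan says.** Section 6.0 of the protocol calls the trial a "prospective, paired, validating confirmatory study". Every patient is examined on both devices: "Point-of-care ultrasound (POCUS) will be performed using both the Siemens ACUSON S2000 (mid-end) and Samsung RS85 (high-end) machines". On who scans, it says "Both ultrasound examinations will be conducted jointly by a GI sonologist and an IBD specialist". The same section then states how a result is fixed: "with findings documented by a research associate and consensus reached by the examiners".

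The section gives probes, presets and fasting advice. It does not say which machine comes first, whether the order varies between patients, how long the gap between scans is, whether the second scan is masked to the first, or whether findings from the first machine are closed before the second is used. No other section supplies these points.

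The rationale (section 2.0) states the aim: to "validate whether mid-end ultrasound machines can reliably match the diagnostic accuracy of high-end machines".

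**The concern.** The primary objective is a within-patient comparison of two machines against ileo-colonoscopy. The evidence for a difference in sensitivity comes from diseased patients in whom one machine detects involvement and the other does not. If examiners have already located thickened bowel on one machine, they know where to look on the other. Some pairs that would have been discordant then become concordant, and the observed difference shrinks.

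Similarity is the favourable result here. Carry-over would favour the hoped-for conclusion, and the results could not separate equivalent machines from shared examiner knowledge. If the order were the same for every patient, machine and order would also be confounded. All this is fixed when the data are collected, so a statistical analysis plan cannot restore independence afterwards.

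**Working it through.** **Plan's own figure.** There is none to reproduce. Section 8.0 says "This is a pilot study and hence we plan to recruit 100 patients" and gives no effect size, power or margin. What follows only illustrates how carry-over acts.

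**Inputs**
- Mid-end sensitivity 80%: the introduction's figure for Crohn's disease from the previous study.
- High-end sensitivity 90%: assumption.
- Diseased patients: 60 of the 100 in the main illustration (assumption), with 50, 70 and 100 as a range.
- Alpha 0.05: section 9.0. Sidedness is not stated; two-sided is assumed.
- A share c of second reads copies the first: assumption, taken at 0, 25% and 50%.
- Discordant cells (high-end only positive / mid-end only positive), two assumptions:
  - reads strongly correlated given disease: 12.5% / 2.5%;
  - reads independent given disease: 0.90 × 0.20 = 18% and 0.10 × 0.80 = 8%.
  - Both give a 10-point difference.

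**Step 1: the observed gap.** A copied read is always concordant, so each discordant cell is multiplied by (1 − c). The observed difference is 10 × (1 − c) points:
- c = 0: 10 points
- c = 25%: 7.5 points
- c = 50%: 5 points

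Either order narrows the gap. At c = 50% with the high-end machine first, mid-end sensitivity is seen as 0.5 × 80% + 0.5 × 90% = 85%. With the mid-end machine first, high-end sensitivity is seen as 85%. Randomising the order changes which machine is affected but does not restore the 10 points.

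**Step 2: exact two-sided McNemar power, 60 diseased**

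| c | cells 12.5% / 2.5% | cells 18% / 8% |
|---|---|---|
| 0 | 0.40 | 0.25 |
| 25% | 0.25 | 0.17 |
| 50% | 0.10 | 0.10 |

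Range for cells 18% / 8%, at c = 0 / 25% / 50%:
- 50 diseased: 0.20 / 0.13 / 0.07
- 70 diseased: 0.30 / 0.21 / 0.12
- 100 diseased: 0.42 / 0.32 / 0.20

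**Step 3: what the possible remedies cost**
- *First scan only.* With randomised order, 60 diseased patients split into about 30 v 30. At 90% v 80%, Fisher exact power is about 0.10. The comparison is free of carry-over but unpaired and weak.
- *One examiner per machine.* Suppose disagreement between examiners adds 5 points to each discordant cell: 12.5% + 5% = 17.5% and 2.5% + 5% = 7.5%. Power with 60 diseased falls from 0.40 to 0.26 with no carry-over at all.

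**The case against.** **The protocol is silent rather than wrong.** It does not say that the same two individuals do both scans, that the order is fixed, or when consensus is reached. A reader might infer that the second result is contaminated and that the machines will look alike, but the text does not support that. One team is the natural reading, order and masking are unstated, and the extent of carry-over cannot be known. What remains is that these are matters of conduct that belong in the protocol, and that the procedure as written permits carry-over.

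**The bias could run the other way.** The examiners know which machine they are using, and the rationale credits the high-end device with better image quality. Expectation could widen the gap. This stands: the net direction and size are unknown.

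**Joint scanning has a merit.** One team on both machines holds operator skill constant, which is useful when comparing devices. This also stands, and it is why separate examiners are a trade-off and not the plain correction.

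**Low power is mostly another problem.** Even at c = 0 the illustration gives only 0.25 to 0.40, so much of the shortfall comes from sample size. Power to detect a difference also does not measure the risk of wrongly concluding similarity. The shrinking gap is the more relevant figure.

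**The ethics section.** A reader might take "ensuring a thorough and objective evaluation of the imaging techniques" in section 10.0 as a claim that the scan procedure is objective. That sentence credits the multidisciplinary team and does not mention the joint scans, so it is no contradiction.

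**Conclusion.** The point holds as a gap in study conduct. Joint scanning with consensus findings, and no stated order, masking or locking, lets the first scan inform the second. This can bias the paired comparison towards agreement, which is the result the study hopes to show. A fixed order, if used, would add confounding of machine with order.

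The size cannot be derived from the protocol. If 25% to 50% of second reads copied the first, a 10-point gap would be observed as 7.5 to 5 points. This rests on the assumed 90% sensitivity and on the copying model, and the power figures rest also on the assumed discordance and number of diseased patients. Expectation bias is not included.

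**What to change.** In section 6.0:
1. Randomise the machine order for each patient.
2. Record the first machine's segment-level findings and lock them with a time stamp before the second scan starts.
3. Record the order and report the paired comparison adjusted for it.
4. Add a sensitivity analysis restricted to first scans.
5. State that any conclusion that the machines match is qualified by shared examiner knowledge.

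The cost is an amendment to the scan procedure, a randomisation list and a separate form for each machine; no extra staff are needed. The limits should be stated too. Randomised order balances carry-over between machines, and locking stops back-editing, but neither removes carry-over. The first-scan-only comparison avoids it at low power (about 0.10 with 30 v 30 diseased).

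**Option, if both examiners can scan alone:** each scans on one machine, unaware of the other's result, with examiner-to-machine assignment randomised and balanced, and the independent reads are compared. This removes carry-over. It adds between-examiner variance that balancing does not remove (0.40 to 0.26 in the example above) and gives up constant operator skill. The protocol describes only joint examination, so whether each examiner can scan alone has to be confirmed first.

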**10.0 ETHICAL JUSTIFICATION OF THE STUDY**

The study titled "Comparing Diagnostic Accuracy of High-End Intestinal Ultrasound Versus Mid-End Ultrasound with Tandem Ileo-Colonoscopy in Inflammatory Bowel Disease (the HUMID Study)" is designed to evaluate the diagnostic accuracy of high-end versus mid-end intestinal ultrasound machines in the context of inflammatory bowel disease (IBD) with ileocolonic involvement. This study aims to address the critical need for effective, cost-efficient diagnostic tools in resource-limited settings.

1. **Patient Benefit and Risk Reduction:**
   - **Non-Invasive Assessment:** The use of both mid-end and high-end ultrasound machines for evaluating bowel conditions provides a non-invasive approach to diagnosis, enhancing patient comfort and safety. This reduces the need for more invasive procedures such as ileo-colonoscopy, which carries risks including bleeding, perforation, and patient discomfort.
   - **Improved Diagnostic Accuracy:** By comparing the diagnostic accuracy of mid-end and high-end ultrasound machines against the gold standard of ileo-colonoscopy, the study aims to identify the most effective and cost-efficient tool for managing IBD. This could lead to better disease management and outcomes for patients.
2. **Advancing Medical Knowledge:**
   - **Innovative Evaluation:** The study explores the comparative efficacy of different ultrasound machines, contributing valuable insights into the utility of mid-end versus high-end devices in clinical practice. This could improve diagnostic protocols and resource allocation in settings with limited access to advanced imaging.
   - **Enhanced Disease Management:** Findings from the study could potentially revolutionize the management of IBD, providing a more accessible diagnostic option that can be widely implemented in resource-constrained environments.
3. **Ethical Study Design:**
   - **Informed Consent:** Participants will undergo a thorough informed consent process, ensuring they are fully informed about the study’s procedures, risks, and benefits. This process ensures that patients can make well-informed decisions regarding their participation.
   - **Minimizing Risk:** The study design prioritizes minimal risk to participants. The use of non-invasive ultrasound techniques, combined with ileo-colonoscopy only when clinically necessary, ensures that unnecessary exposure to invasive procedures is minimized.

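### Ileo-colonoscopy, the reference standard, is given only if clinically indicated, and nothing fixes that decision before the two scans, so the accuracy estimates are open to partial-verification bias

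*Protocol*

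**What the plan says.** The protocol describes the reference standard in two ways.

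**Conditional.** Section 6.0: "Ileo-colonoscopy will be performed on the same or following day if clinically indicated, providing the diagnostic gold standard". Section 10.0, item 3, offers the same condition as an ethical safeguard: "combined with ileo-colonoscopy only when clinically necessary, ensures that unnecessary exposure to invasive procedures is minimized".

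**Apparently universal.** The title describes ileo-colonoscopy as done in tandem with the ultrasound. Section 5.0 reads "Cross-sectional study, follow up until ileo-colonoscopy (same or next day", which makes colonoscopy the end of every patient's follow-up.

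Eligibility does not settle the matter. Section 4.0 admits "Adult patients (18-75 years) with a confirmed diagnosis of IBD (CD or UC) involving colon and/or terminal ileum" in outpatient or inpatient care, with no requirement that a colonoscopy be planned. Section 6.0 expects a broad clinical spectrum: "Patients will be categorized into three groups: flare/relapse, response to new therapy, and clinically quiescent disease". An IBD specialist takes part in both scans, and no section says when the decision to scope is made or whether it is blind to the scan results.

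The Introduction reports that in the earlier mid-end study ultrasound influenced management, "helping to avoid colonoscopy in more than half of the cases". Section 7.0 makes management altered by the ultrasound an outcome of this study too.

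**The concern.** Sensitivity and specificity can be computed only in patients who have a reference result. If scan-positive and scan-negative patients are scoped at different rates, the scoped patients are a sample selected by the tests under evaluation. The proportions observed in them then do not estimate the true ones. This is partial-verification bias.

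The protocol gives reason to expect it. Its own earlier study credits ultrasound with sparing patients colonoscopy. If a spared colonoscopy counts as altered management, the same event adds to the second outcome and removes a patient from the first. At stake are the absolute accuracy figures, possibly the comparison between machines that is the primary objective, and the number of the 100 patients who can contribute at all.

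This is a matter of eligibility and procedure. An analysis plan cannot recover a scope decision that was not recorded before scanning.

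**Working it through.** **Inputs from the protocol.** Mid-end accuracy in the Introduction: the earlier study "had a sensitivity of 80% and a specificity of 94.4% for CD, and a sensitivity of 80.8% and a specificity of 92.8% for UC". Sample size in section 8.0: 100, stated without a calculation, so there is nothing to reproduce; the point does not depend on it. The protocol gives no verification rates, prevalence of active disease or high-end accuracy. All of these are assumptions below.

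**1. One machine.** Let v+ and v− be the shares of scan-positive and scan-negative patients who are scoped.

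- Apparent Se = Se·v+ / [Se·v+ + (1−Se)·v−]
- Apparent Sp = Sp·v− / [Sp·v− + (1−Sp)·v+]

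With v+ = v− these return the true values. Take Se 0.80 and Sp 0.94 (close to the protocol's figures) and 60% active disease.

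| v+ / v− | Apparent Se | Apparent Sp | Share scoped |
|---|---|---|---|
| 0.7 / 0.3 | 0.56/(0.56+0.06) = 90% | 0.282/(0.282+0.042) = 87% | 0.6×0.62 + 0.4×0.324 = 50% |
| 0.3 / 0.7 | 0.24/(0.24+0.14) = 63% | 0.658/(0.658+0.018) = 97% | 0.6×0.38 + 0.4×0.676 = 50% |

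With the protocol's exact mid-end values and v+ / v− = 0.9 / 0.3:

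- CD: Se 0.72/0.78 = 92.3%; Sp 0.2832/0.3336 = 84.9%.
- UC: Se 0.7272/0.7848 = 92.7%; Sp 0.2784/0.3432 = 81.1%.

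At 50% prevalence the CD case leaves 100 × (0.5×0.78 + 0.5×0.3336) ≈ 56 patients scoped, about 17 of them without disease.

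**2. The machine difference.** Assume true sensitivity of 90% (high-end) and 80% (mid-end). Among diseased patients, if both kinds of discordant pair are scoped at the same rate w, then

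apparent difference = true difference × w / (overall scoping rate among the diseased).

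*Either positive scan raises scoping from 30% to 90%.* With the machines independent given disease, the cells are both positive 0.72, high-end only 0.18, mid-end only 0.08, both negative 0.02. Overall rate = 0.9×0.98 + 0.3×0.02 = 0.888. Apparent values are 0.81/0.888 = 91.2% and 0.72/0.888 = 81.1%, a gap of 10.1 points; the ratio stays at 1.125. Specificity, if truly 94.4% on both, falls to 0.3149/0.3653 = 86.2% on both.

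*Discordant scans scoped at 90%, concordant at 40%.* With correlated machines (cells 0.78, 0.12, 0.02, 0.08), overall rate = 0.4×0.86 + 0.9×0.14 = 0.47. Apparent values are 0.42/0.47 = 89% and 0.33/0.47 = 70%, a gap of 19 points.

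The contrast comes from the scoping rule, not from the choice of cells. Swapping them, the first rule on the correlated cells gives 0.10×0.9/(0.9×0.92 + 0.3×0.08) = 0.09/0.852 = 10.6 points. The second rule on the independent cells gives 0.10×0.9/(0.4×0.74 + 0.9×0.26) = 0.09/0.53 = 17 points.

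**The case against.** **The protocol never says that the scans drive the decision.** Section 6.0 times the procedure, not the order. The title, section 5.0 and the exclusion of patients with contraindications to colonoscopy all fit a colonoscopy planned beforehand. This stands: a reader might infer that the estimates are certainly biased, but the documents support only that they will be if scoping depends on the scans or their correlates. If scoping were unrelated to either, sensitivity and specificity would be unbiased, though some patients would still lack a reference result.

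**The primary objective is a paired comparison, which can survive.** This also stands. The 19-point gap is one chosen pattern; a simpler one leaves the gap at about 10 points. The protocol does not say which applies.

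**Predictive values may be spared.** If verification depends only on one machine's result, that machine's PPV and NPV among scoped patients are unbiased. This need not hold when both scans influence the decision.

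**A reader might infer that fewer than half of the 100 will be scoped.** The earlier study's avoidance figure does not establish that. It comes from a different study, and here colonoscopy is the reference standard and the end of follow-up. The share is unknown.

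**Section 9.0 names no correction.** That can be left to an analysis plan and is not the complaint. What an analysis plan cannot supply is a scope decision made independently of the scans.

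**Conclusion.** The concern holds in conditional form. Sections 6.0 and 10.0 conflict with the title and section 5.0, and as written the protocol leaves the reference standard open to selection by the tests it is meant to judge. The Introduction makes such selection likely; no section states it.

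If it occurs, absolute sensitivity and specificity can move materially in either direction: in the worked cases, sensitivity from 80% to between 63% and 90%, and specificity from 94% to between 87% and 97%. These rest on assumed scoping rates of 70% and 30%. The machine difference may be almost intact or nearly doubled, depending on how discordant scans are handled. An unknown share of the 100 would not contribute to the accuracy outcome.

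**What to change.** 1. Reconcile the title and sections 5.0, 6.0 and 10.0 on who receives ileo-colonoscopy.
2. In section 4.0, limit the accuracy cohort to patients whose ileo-colonoscopy was already ordered on clinical grounds before any study scan. Record the order and its indication before scanning. The indication itself remains a clinical decision.
3. In section 8.0, count the 100 as patients with both scans and ileo-colonoscopy.
4. For any enrolled patient who ends up without colonoscopy, report verification rates by the results of both scans. Give a verification-bias-corrected estimate as a sensitivity analysis only: with few scoped scan-negative patients the weights would be unstable, and the correction assumes that scoping is explained by the recorded variables.

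The cost is an amendment to eligibility, a pre-scan form entry and a little extra reporting; no procedure is added. The downside is fewer clinically quiescent patients, so the accuracy figures apply to patients already due for colonoscopy, and possibly slower recruitment.
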